## Abstract

**Background:**

The Government of Cambodia established the village health support groups (VHSGs) in 2003 to facilitate primary healthcare activities, including maternal and child health (MCH) services. However, VHSGs face several challenges that hinder them from performing optimally, including a lack of regular structured training and remuneration and limited and inconsistent support and supervision from the health centers (HCs). This implementation research aims to develop, implement, and evaluate a digital health intervention to improve the performance of VHSGs through better support and supervision and increase the MCH service coverage in rural Cambodia.

**Methods:**

i-MoMCARE, a two-arm cluster randomized controlled trial, will be conducted between 2022 and 2025. Five operational districts (ODs) have been randomized to an intervention arm and the other five ODs to the control arm. The intervention will last for 24 months. Around 200 VHSGs in the intervention arm will be equipped with a mobile application as a job aid and 20 HC staff with a web interface to improve support and supervision of VHSGs. The potential beneficiaries will include pregnant women, mothers, and children under 2 years old. We will measure the outcomes at baseline and endline. The primary outcomes will consist of a composite MCH index constructed from maternal and newborn care indicators, child immunization, and treatment of under-two children. Secondary outcomes will include coverage of selected MCH services. We will conduct the intention-to-treat and per-protocol analyses. We will conduct qualitative interviews with selected beneficiaries and stakeholders to evaluate the intervention’s acceptability, feasibility, and scalability. We will also conduct a cost-effective analysis using decision-analytic modeling incorporating a societal perspective that explores different time horizons, intervention effects, and when scaled up to the national level.

**Discussion:**

i-MoMCARE is expected to increase MCH service access and coverage in rural Cambodia. It will contribute to advancing digital health use in primary healthcare interventions, which remains in its infancy in the country. Furthermore, the study findings will be a valuable addition to a growing body of literature on the effectiveness and feasibility of mobile health to improve coverage of MCH services in rural low- and middle-income country settings.

**Trial registration:**

ClinicalTrial.gov NCT05639595. Registered on 06 December 2022.

**Supplementary Information:**

The online version contains supplementary material available at 10.1186/s13063-023-07724-z.

## Background

Cambodia’s maternal mortality ratio (MMR) dropped from 488 in 2000 to 168 in 2016 and 154 in 2021 per 100,000 live births [1]. However, the figure remains notoriously higher than that in other countries in Southeast Asia [2]. Further effort is required to achieve the global MMR target in the Sustainable Development Goals at less than 70 per 100,000 live births by 2030 [3]. Likewise, the infant mortality rate (IMR) substantially decreased by 67%, from 79 deaths in 2000 to 26 deaths in 2016 and 12 in 2021 per 1000 live births [1]. The rate, however, remains higher than that in the neighboring countries, except for Laos (40 deaths per 1000 live births) and Myanmar (39 deaths per 1000 live births) [2].

In Cambodia, despite the drop in the country’s average MMR and IMR, urban and rural disparities persist within the country, stemming from inequity in health service accessibility and utilization, making maternal and child death a remaining public health priority [4, 5]. The primary underlying factors associated with maternal and child deaths include inadequate affordable and accessible primary healthcare services, poor-quality services and hygiene, and a lack of skilled health staff [6]. No woman or child should suffer or die from preventable causes. However, many children’s and mothers’ lives are being lost, especially at birth and during the first month of life [7], especially in rural areas of the country. Increasing coverage of and access to maternal and child health (MCH) services in rural areas is imperative to overcome the gaps in MCH care and improve universal health coverage (UHC).

Over the years, various initiatives and interventions have been put in place by Cambodia’s Ministry of Health (MOH), aiming to reduce maternal and child mortality across the country. The interventions are in line with the 2010–2015 Fast-Track Initiative Road Map for Reducing Maternal and Newborn Mortality [8], the 2017–2020 National Strategy for Reproductive and Sexual Health in Cambodia [9], and the 2016–2020 Emergency Obstetric & Newborn Care Improvement Plan [10]. These guiding papers outline effective initiatives to save the lives of women and children in Cambodia. Despite successful interventions, limited human and financial resources are a significant constraint in expanding these life-saving health initiatives that may effectively reduce maternal and newborn mortality, especially in hard-to-reach and resource-limited settings.

In recent years, tapping on the breakthrough of technological advancement, digital health—the broad scope of which includes mobile health (mHealth), health information technology, wearable devices, telehealth and telemedicine, and personalized medicine—has become the mainstream in the public health arena [11]. Digital health has been used to improve MCH in the Global North, such as in Canada [12] and Australia [13], and in the Global South, including China [14], India [15], and Sub-Saharan Africa [16, 17]. Digital health interventions have successfully reduced maternal and child deaths, especially in low- and middle-income countries (LMICs), by providing job aids to primary healthcare workers.

The Innovative Mobile Technology for Maternal and Child Health Care (*i-MoMCARE*) is a digital health intervention aiming to increase the coverage of and access to MCH services for pregnant women and their children in rural communities in Cambodia. We will fully adapt the Innovative Mobile-phone Technology for Community Health Operations (ImTeCHO), an innovative model developed, successfully implemented, and evaluated by SEWA Rural in Gujarat, India [18]. This study will build on Cambodia’s well-established and well-structured healthcare system, increased Internet coverage, and the sharp rise in smartphone adoption [19] to implement innovative mobile technology intervention. On the one hand, *i-MoMCARE* will provide village health support group (VHSG) access and training on mobile-based job aid (the mobile application) to facilitate their work with pregnant women and mothers in the villages. Specifically, with the mobile application, VHSGs can register pregnant women and mothers, schedule health care appointments, develop a digital record of the medical history of pregnant women and mothers, show educational videos to pregnant women and mothers, and alert HC staff on high-risk cases. On the other hand, *i-MoMCARE* will offer health center (HC) staff access to the web interface to track VHSGs’ activities and clients’ medical history and screen for complications and referrals.

VHSGs are the bedrock of Cambodia’s health system, particularly where access to health services is limited and trained health professionals are scarce. They are central in providing and facilitating healthcare services to people, including pregnant women and under-five children living in rural communities. In Cambodia, long distances to health facilities and insufficient education for women of reproductive age are among the critical determinants of poor health outcomes, predominantly in rural communities where the demand for MCH services is higher than in urban areas [20, 21]. VHSGs could help overcome the long distance to health facilities with mobile technology. Hence, *i-MoMCARE* will improve women’s understanding and access to antenatal care (ANC), safe delivery by skilled health personnel, postnatal care (PNC), and child immunization, reducing high-risk cases and maternal and child deaths. This study is the first to be implemented in Cambodia, contributing to advancing digital health use in MCH interventions, which remain in their infancy.

The general objective of this study is to develop, test, implement, and evaluate the applicability and efficacy of the *i-MoMCARE* to support VHSGs and HC staff in rural communities to increase the coverage of and access to MCH services in Cambodia. The specific objectives of this study include the following: (1) to identify gaps in MCH care through conducting a literature review, consulting with local stakeholders, and qualitative need assessments and gap analyses to understand the barriers to accessing MCH services provided or facilitated by VHSGs; (2) to identify technology components that provide resolutions to fill in the gaps in MCH care services; (3) to pilot and qualitatively evaluate the operational delivery of the *i-MoMCARE* intervention; (4) to implement the *i-MoMCARE* intervention among VHSGs and HC staff; (5) to qualitatively evaluate the acceptability, feasibility, and usefulness of the *i-MoMCARE* intervention; (6) to quantitatively evaluate the effectiveness of *i-MoMCARE* in improving the MCH coverage, MMR, IMR, and other key indicators; and (7) to evaluate the cost-effectiveness of *i-MoMCARE* for adopting and scaling up the intervention in Cambodia.

## Methods

We will conduct this implementation research between 2022 and 2025 in 10 provinces. The study protocol adheres to the Standard Protocol Items: Recommendations for Interventional Trials (SPIRIT) diagram (Fig. 1), the Consolidated Standards of Reporting Trials (CONSORT) study flow chart (Fig. 2), and the SPIRIT Checklist (Additional file 1).

**Fig. 1 Fig1:**
[figure not shown]
The Standard Protocol Items: Recommendations for Interventional Trials (SPIRIT) diagram

**Fig. 2 Fig2:**
[figure not shown]
CONSORT study flow chart. HC, health center; MCH, maternal and child health; NMCHC, National Maternal and Child Health Center; OD, operational district; SES, socioeconomic survey; VHSG, village health support group

### Study design

This study is a two-arm stratified multi-stage, cluster randomized controlled trial (RCT). We will deploy digital health technology in five provinces. The five provinces have been selected based on the composite index of the MCH indicators and socioeconomic status (SES) indicators and consultation with the National Maternal and Child Health Center (NMCHC) of Cambodia’s MOH. We will conduct a literature review and gap analysis using in-depth interviews (IDIs), key informant interviews (KIIs), and focus group discussions (FGDs) with key stakeholders to acquire information necessary for introducing and adapting the digital health technology, successfully deployed in Gujarat, India, to the Cambodian rural settings.

### Randomization

The randomization will be done at the operational district level (cluster), the third tier of Cambodia’s health system. To address the issue of contamination that may arise and maintain comparability between the two arms (balanced randomization) at baseline, we performed a matched-pair selection of 10 provinces (five for each arm) out of the 25 provinces in Cambodia based on similar levels of MCH-SES index and NMCHC’s recommendations (Table 1). We used the principal component analysis approach [22] to construct the provinces’ MCH-SES index from a basket of indicators of ANC, delivery, and PNC from the Cambodia Demographic and Health Survey (CDHS) 2021 [4] and indicators of socioeconomic status from the National Population Census 2019 [23] and Cambodia Socioeconomic Survey 2019 (CSES) [24]. The indicators from CDHS 2021 included the proportion of pregnant women attending at least four ANC, the proportion of women delivering in a health facility, the proportion of women having a PNC visit in the first 2 days after delivery, the proportion of fully vaccinated (basic antigen) children aged 12–24 months, the proportion of fully vaccinated (according to the national schedule) among children aged 12–24 months, and proportion of children aged 12–24 months without vaccinations. The indicators from the population census 2019 included population density, literacy rate of the population aged 7 years and older, the proportion of the population aged 15 years and older with secondary education or higher, the proportion of households with electricity, and the proportion of households with piped water in a dwelling, while median monthly income per capita in thousand Khmer riels was from the CSES 2019.

**Table 1 Tab1:** List of matched-pair provinces with their respective MCH-SES indices

Pair	Matched province	MCH-SES index	Matched provinces	MCH-SES index
1	Kampong Speu	1.11	Kampong Chhnang	1.38
2	Pailin	0.37	Pursat	0.12
3	Kampot	− 0.17	Preah Sihanouk	0.15
4	Oddar Meanchey	− 1.07	Kampong Thom	− 1.34
5	Preah Vihear	− 2.75	Ratanak Kiri	− 7.77

*MCH* Maternal and child health, *SES* Socioeconomic survey

As shown in Fig. 2, we will randomly select one operational district from each province after visiting study sites and excluding ODs in the provincial town (urban area) and those without Internet coverage. Within each pair of the 10 selected provinces, we will randomly assign one operational district to an intervention arm and the other to a control arm using Excel (Microsoft). Blinding to the participants, including HC staff, VHSGs, and the beneficiaries, would not be possible in this community-based intervention study. We also have no plan to make the allocation blind to the outcome assessors and data analysts. We will then randomly select two HCs from each operational district after excluding those covering less than 10 villages and without Internet coverage. In Cambodia, HCs provide a minimum package of activities, such as preventive and primary curative services, each serving approximately 10,000 to 20,000 people in villages under its coverage [25]. The number of HC staff may vary between eight and 11. The staff members typically include medical doctors (uncommon), midwives, nurses, and supporting staff.

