#### Quantitative data

##### Mobile and web-based applications

The process indicators will be collected from the web interface of the *i-MoMCARE* program during the intervention. Data from the mobile application will be linked to the web interface and stored in encrypted cloud storage hosted by the UHS. Given the high sensitivity of personal health data, we will develop a data management strategy for the data collected by the mobile application and web interface to ensure the data security and privacy and confidentiality of the participants. Data will be backed up regularly into encrypted computers. Only research team members will have access to the data.

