##### Household survey and anthropometry measures

We will conduct household surveys at baseline and endline to measure the primary and secondary outcomes of interest in control and intervention arms. We have developed a household survey questionnaire (Additional file 2) based on the tools used in the Cambodia Demographic Health Survey (CDHS) 2021 and the National Guidelines for Implementing the Service Package of Antenatal, Delivery, and Postnatal Care [4, 29]. We will pre-test the tools before the data collection. Mothers of children aged 6–24 months and pregnant women aged 18–49 years will be eligible to participate in the surveys. The survey will collect household demographic information, durable assets, access to ANC, delivery, and PNC services, health insurance coverage, social health protection, health expenditures, and child anthropometric information. We will use an online platform to store the data and an electronic tablet installed with the data collection application equipped with Internet access to enter the data by trained interviewers. A village-level household population list from the population census in 2019 will be used as a sampling frame for household selection.

We will measure weight and height and check for edema of the eligible children (aged 6–24 months) to measure their nutritional status during the household survey. Weight will be measured in kilograms (kg) using the United Nations Children’s Fund (UNICEF) Uniscale with a precision of 100 g (one decimal point). Height will be measured using a length board from UNICEF in centimeters with a precision of one millimeter. The enumerators will measure height and weight twice. A research team member with a child nutrition background will train the interviewers to perform the anthropometric measurements. All enumerators will practice the anthropometric measurements during the pre-test. They will be instructed to calibrate the weighing scale before collecting data.

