##### Interim analyses

A data analyst masked to intervention allocation will conduct interim analyses.

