### Oversight and monitoring

#### Composition of the coordinating center and trial steering committee

The coordinating center will be based at UHS, the primary implementing organization. The steering committee will comprise representatives of NMCHC, NUS-SSHSPH, UHS, and key stakeholders working on MCH in Cambodia (e.g., WHO, UNICEF, UNFPA, USAID, and local NGOs). Data will be stored and managed by the team at UHS, with technical support from NUS-SSHSPH and Argusoft. The research team from NUS-SSHSPH will be responsible for data analyses. The steering committee will adjudicate the endpoints and develop the findings dissemination plan in consultation with the data monitoring committee. During the trial preparation phase, the steering committee will meet every month, and during the intervention, the committee will meet every quarter (or ad hoc meeting). The research team will produce meeting reports to update research progress or report any issues during the project implementation.

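### No masking is planned for outcome assessors or data analysts, without a reason and in conflict with the masked interim analyst, although key primary outcomes rest on mothers' reports of VHSG contact

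*Protocol article*

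**What the plan says.** On participants, the Randomization section of the protocol article gives a reason for the open design: "Blinding to the participants, including HC staff, VHSGs, and the beneficiaries, would not be possible in this community-based intervention study". On the people who measure and analyse, it adds only: "We also have no plan to make the allocation blind to the outcome assessors and data analysts". No reason follows, and interim and final analysts are not distinguished.

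The Interim analyses section consists of one sentence: "A data analyst masked to intervention allocation will conduct interim analyses". The section on the coordinating center and steering committee says "The research team from NUS-SSHSPH will be responsible for data analyses" and is silent on masking. The section on adherence strategies gives regular supervision and interim analyses to researchers of the same university.

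On measurement, the household survey section says "We will conduct household surveys at baseline and endline to measure the primary and secondary outcomes of interest in control and intervention arms", with electronic tablets used "to enter the data by trained interviewers". Eligible respondents include mothers of children aged 6–24 months. The Data collection and management section places data collection under the department that leads implementation of the intervention.

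**The concern.** Participants and VHSGs cannot be masked in a trial of this kind. That does not settle the matter for enumerators and analysts, and the article states a decision about both without defending it.

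The outcomes make the decision matter. One primary outcome is whether a VHSG made two or more home visits in the week after delivery. Another is whether a VHSG explained newborn danger signs in that week. With children aged 6–24 months at interview, the mother is recalling a week that lies months back, and such answers can respond to how a question is probed. An enumerator who knows that a district has the intervention, and works under the implementer's supervision, may probe differently there.

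For the analysis, the document says two different things about masking. A reader cannot tell whether the final analysis will be done with the arms known.

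**Working it through.** **1. The statements on analysts, side by side.**

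| Section | Who | Masking stated |
|---|---|---|
| Randomization | Outcome assessors and data analysts | None planned |
| Interim analyses | A data analyst | Masked |
| Coordinating center and steering committee | University research team, data analyses | Not stated |

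The first row covers data analysts without exception and the second describes a masked one. They agree only if the first is read as applying to the final analysis alone, which the text does not say. The second row does show that the investigators regard a masked analyst as workable.

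**2. How much of the primary outcome set depends on reported VHSG contact.** Outcomes 1 and 2 of three do so entirely. For the index, the Primary outcomes section says that the three components are equally weighted and gives factors 1/4, 1/2 and 1/3 for four, two and three sub-components. Read as a mean of component means:

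| Component | Weight per item | VHSG-specific items | VHSG weight |
|---|---|---|---|
| Antenatal and postnatal care | 1/3 × 1/4 = 1/12 | 1 of 4 (VHSG visits in pregnancy) | 1/12 |
| Immunization | 1/3 × 1/2 = 1/6 | 0 of 2 | 0 |
| Treatment | 1/3 × 1/3 = 1/9 | 3 of 3 (care or oral rehydration from VHSGs) | 3/9 |

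The sum is 1/12 + 4/12 = 5/12, or 41.7%.

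**3. What difference-in-difference does with the bias.** Let b be the over-reporting in each arm at each survey. The expected estimate is

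true effect + (b intervention, endline − b control, endline) − (b intervention, baseline − b control, baseline).

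Only a between-arm gap already present at baseline cancels. A gap that arises at endline passes in full into the two VHSG-contact outcomes. If all VHSG items shift alike, 5/12 of it passes into the index.

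**4. Size, by assumption only.** The document gives no misreporting rate. A differential shift of 3–5 points in the VHSG items would move the index by 3 × 5/12 = 1.25 to 5 × 5/12 = 2.1 points.

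To judge the effect on false positives for a single binary item, assume no true effect, 70% coverage, 929 mothers per arm in five clusters, ICC 0.02, one endline comparison and a normal approximation. The cluster size is 929/5 = 185.8, so the design effect is 1 + 184.8 × 0.02 = 4.696. The effective number is 929/4.696 = 197.8 per arm, and the standard error is √(2 × 0.21/197.8) = 0.046. If a share of the uncovered 30% in the intervention arm is over-reported:

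| Share over-reported | Bias (points) | Two-sided type I error |
|---|---|---|
| 5% | 1.5 | about 6% |
| 10% | 3.0 | about 10% |
| 20% | 6.0 | about 26% |

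The 70% is borrowed from the planning index. No level is given for VHSG contact, so this shows sensitivity and is not an estimate.

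**5. Sample size is untouched.** The plan's figure reproduces with 70% against 83%, two-sided 5% and 85% power: (1.960 + 1.036)² × (0.21 + 0.1411)/0.13² = 186.53 per arm. Multiplying by 1 + 199 × 0.02 = 4.98 gives 928.9, that is 929 per arm and 1858 in total. Then 1858 × 1.05 = 1950.9, or 1951. No term in this depends on masking.

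**The case against.** The trial is openly described as an open cluster randomized trial, so the lack of masking is disclosed. Enumerator masking can only be partial: whole districts are allocated, respondents know what they received, and answers about VHSG contact may reveal the arm. A masked enumerator also does nothing about a mother's own recall or courtesy bias. On the analyst side, the article already names intention-to-treat with difference-in-difference as the main approach. The detailed rules for adjustment, per-protocol sets and imputation belong in an analysis plan that is not shown, and the adjustment trigger uses baseline data. The adherence section also describes the analysing university as not an implementing organization, although the cost-effectiveness section lists it among the implementing teams.

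Most of this stands, and it limits the point without removing it. Partial masking still prevents probing driven by prior knowledge of the arm, and none of these arguments reconciles the two statements on analysts.

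Several stronger readings are tempting but unsupported:

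- A reader might infer that every survey coverage outcome is self-reported. The article does not say how vaccination, facility delivery or visit counts are ascertained.
- A reader might set an assumed bias of 3–5 points against the planned 13 points (3/13 = 23%, 5/13 = 38%). The planning index consists of antenatal visits, early postnatal visits and immunization. It has no VHSG-contact item, so the ratio compares unlike things.
- A reader might call the bias fully avoidable at almost no cost. The residual bias above, and pairs that span different provinces, speak against that.
- A reader might take bias in favour of the intervention as established. The direction is plausible, but the document offers no evidence for it.

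**Conclusion.** The point holds as a design choice that should be changed and a contradiction that should be resolved. Leaving assessors and analysts unmasked is stated without justification, the interim analysis is described differently, and the final analysis has no stated masking. The exposure is concentrated in two of the three primary outcomes and in 5/12 of the index weight. The latter figure assumes that the index formula means an equally weighted mean of the three components. Bias that arises only at endline would survive the planned analysis. Its size and direction cannot be derived from the document, and the ranges in the working rest on assumed misreporting rates.

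**What to change.** Replace the sentence in the Randomization section with text to this effect: enumerators will not be told the allocation and will use the same standardised questions in both arms; where travel allows, the same teams will survey both districts of a pair; final analysts will work with arms coded A and B until the primary analysis code and the analysis sets are locked.

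Align the Interim analyses section and the section that assigns the data analyses, so that masking is stated once for interim and once for final analyses. Check the adherence section as well, because analysts who also supervise adherence may learn the allocation.

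Add to the limitations that enumerator masking is partial and that respondents' own recall or courtesy bias remains.

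Cost: field instructions, data-release wording, someone outside the analysis to hold the arm key, and some travel between provinces where teams cover both districts. The document gives no costing, but no extra staff should be needed. Sample size, power and alpha do not change.

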#### Phase 2: Cluster randomized controlled trial

An open cluster randomized controlled trial will be conducted to evaluate the mobile application utilization and the intervention’s effectiveness in improving MCH service uptake and outcomes aided by the mobile application. We have estimated that approximately 200 VHSGs will be included in the intervention arm across five operational districts (ODs) in five provinces. Figure 2 shows a flowchart of VHSGs and the HC staff selection process for the intervention and control arms. Figure 4 illustrates the map of the 10 provinces proposed as study sites, five of which will be assigned to the intervention arm after randomly selecting one OD from each. We will randomly select two HCs covering approximately 10 villages from each OD. Two HC staff will be purposively selected from each HC in the intervention arm.

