##### Control arm

As discussed in the study design, HCs in the control arm will be randomly selected from their ODs. The randomization process will be similar to those in the intervention arm. All villages under the HC’s catchment areas in the control arm will continue to receive MCH standard care provided by the government and NGOs and facilitated by VHSGs. VHSGs in the intervention and control arms will receive refresher training on maternal, neonatal, and childcare to avoid ethical issues that may arise and ensure that any change in outcomes in the intervention arm is due only to the *i-MoMCARE* intervention.

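### Health centres are excluded and drawn only after each district's arm is assigned in an open trial, with nothing to shield that step from knowledge of the arm; bias is possible but not shown, and the order is cheap to change

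*Protocol article*

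**What the plan says.** The Randomization section gives the steps in order. District selection comes first: "we will randomly select one operational district from each province after visiting study sites and excluding ODs in the provincial town (urban area"), and ODs without Internet coverage are also removed at that stage. Arm assignment within province pairs comes next: "we will randomly assign one operational district to an intervention arm and the other to a control arm using Excel (Microsoft"). The HC step follows: "We will then randomly select two HCs from each operational district after excluding those covering less than 10 villages and without Internet coverage".

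The Phase 2 section keeps the same order, with OD selection and arm assignment described before the HC draw. The Control arm section describes the HC draw under its arm label, "HCs in the control arm will be randomly selected from their ODs", and adds that the process resembles the one in the intervention arm.

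On blinding, Phase 2 says "An open cluster randomized controlled trial will be conducted to evaluate the mobile application utilization". The Randomization section says "Blinding to the participants, including HC staff, VHSGs, and the beneficiaries, would not be possible in this community-based intervention study" and "We also have no plan to make the allocation blind to the outcome assessors and data analysts".

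The tense differs between sections. The Abstract reports the allocation of the ten ODs as done, whereas the Randomization section describes it as still to come. The HC draw is in the future tense throughout.

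**The concern.** In a cluster trial, random assignment protects the comparison only for units whose membership was settled before, or independently of, the assignment. Here the OD is randomised, but the HCs that decide which villages and mothers are surveyed are chosen later. A random draw is neutral with respect to the list it is drawn from. It does not correct a list that was trimmed differently in the two arms.

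Of the two HC criteria, the village count leaves little room for judgement. Internet coverage at an HC is less clear-cut, and the article gives no threshold or data source. It also matters for day-to-day delivery only where the mobile application and web interface must run, that is, in the intervention arm. The Strengths and limitations section names differing mobile networks as a technical challenge. Someone who knows the arm therefore has a practical reason to look harder at connectivity in intervention districts.

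If that happened, better-connected and perhaps more accessible HCs would be over-represented in one arm. Pair matching would not correct this, because it uses province-level indices. There are only two HCs per OD and ten per arm, so a few differing exclusions could change an arm's make-up.

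**Working it through.** **1. Does the order depend on the reading?** Three places bear on it.

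- Randomization: OD exclusions, OD draw, arm assignment, then HC exclusion and draw.
- Phase 2: the same sequence.
- Control arm: the HC draw is described under a known arm label.

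If the Abstract is current, arms are already known while the HC draw is still to come. All of this agrees with HC selection after allocation. One gap remains: the site visits before the OD draw might already have recorded HC connectivity. The text does not say.

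**2. Where could the arm influence inclusion?**

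- OD-level Internet exclusion: before allocation, so not exposed.
- HC village count: an objective count, so little room.
- HC Internet coverage: applied after allocation with no stated source or shield, so exposed.
- HC draw: random, so not exposed if done once from a fixed list.
- Households: drawn from a 2019 census list (household survey section), which predates allocation.

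The exposure is essentially the third item.

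**3. The plan's own sample size, and whether reordering changes it.** Inputs from Sample size: 70% coverage, effect 13% (read as 13 percentage points, so 70% against 83%), ICC 0.02, cluster size 200, 95% confidence (taken as two-sided 5%), power 85%.

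- Per arm, unclustered: (1.960 + 1.036)² × (0.70×0.30 + 0.83×0.17) / 0.13² = 186.53
- Design effect: 1 + (200 − 1) × 0.02 = 4.98
- Per arm: 186.53 × 4.98 = 928.9, i.e. 929; both arms 1858
- With the 5% allowance: 1858 × 1.05 = 1950.9, i.e. 1951

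The stated figures reproduce. Screening HCs first still gives 10 ODs × 2 = 20 HCs and the same cluster size, so every line above is unchanged.

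**4. An illustration of size.** The article gives no between-HC variation. Assume it equals the between-OD SD implied by the plan:

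- SD = √(0.02 × 0.70 × 0.30) = 0.0648, or 6.5 points

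Suppose a fraction f of HCs is dropped for poor connectivity in one arm only. Let r be the correlation between connectivity and MCH coverage, under a normal model:

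- Shift in that arm's mean = r × SD × φ(z_f) / (1 − f)

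| f | r = 1 | r = 0.5 | r = 0.3 |
|---|---|---|---|
| 20% | 2.3 points | 1.1 points | 0.7 points |
| one third | 3.5 points | 1.8 points | 1.1 points |

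The values of f and r are assumptions, and the shift scales in proportion to the SD. For a given f and SD, the r = 1 column is the upper bound, and it also requires exclusion in one arm only. These are shifts in level. The Analysis plan uses difference-in-difference between baseline and endline, which removes a constant level difference. What could survive is a difference in trend over the 24 months. The article has no figure for that.

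**The case against.** The strongest reply is that the article describes equal treatment. One rule is stated for every OD, the draw is random, and the Control arm section says the process is similar to that in the intervention arm. Connectivity has already been screened at OD level before allocation, so only variation within connected, non-urban districts remains. A condensed article may also leave the connectivity threshold and data source to the full protocol, so their absence does not show that the screen is discretionary. All of this stands, and it limits the point to a possible bias in a narrow step.

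It does not remove the point. A common criterion protects the comparison only if it is applied without regard to the arm, and the article itself fixes an order in which the arm comes first.

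Three stronger readings are tempting, and the article does not support them.

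- *Intervention HCs will be screened more strictly.* Nothing in the text says so.
- *Those who screen HCs are known to be unblinded.* The non-blinding statements cover participants, outcome assessors and data analysts. The article does not say who screens HCs.
- *The effect estimate is off by two to three points.* Those figures need one-arm exclusion and a perfect link between connectivity and coverage. They are also level shifts, so they should not be set directly against the 13-point planned effect.

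**Conclusion.** The order of steps is as described, and no stated safeguard separates HC eligibility from knowledge of the arm. This is an avoidable opening for selection bias, not a demonstrated bias. It rests on reading the Randomization sequence literally and on the article not mentioning any earlier HC list.

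The size of any bias in the final estimate cannot be derived from the document, and its direction is not settled either: better-connected areas might improve faster, or might have less room to improve. The planned sample size and power are unaffected.

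The point is worth acting on because the protection is specific and nearly free if taken before allocation. It would be wrong to say that it costs nothing in all circumstances: if the ODs have already been allocated, the simple reordering is no longer available.

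**What to change.** **If arms are not yet drawn.** Change the order in the Randomization section. Apply the two HC exclusions in all ten ODs from one data source that does not depend on the arm, for example operator coverage data or the site visits made before allocation. Draw two HCs per OD and lock the list. Only then make the within-pair arm draw.

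**If arms are already drawn, as the Abstract states.** Apply the same written criteria to the same kind of arm-independent source. Have someone who sees only coded OD labels make the exclusions and the draw. Coding alone is not enough: if staff who know the arm collect the connectivity data, any difference is already in the data. Report the HCs screened and excluded, with reasons, by arm.

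In either case, reconcile the tense of the Abstract with that of the Randomization section, so that a reader can tell which route applies.

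**Cost.** HC lists are needed slightly earlier, or the screening step must be masked. The 20 HCs, the 1951 mothers and the power stay as planned.
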